## 3. Discussion

This protocol presents a randomized trial aimed at evaluating the efficacy and safety of an exercise program designed for improving the quality of life in people who had undergone THR or TKR. Most patients report successful long-term outcomes and reduced or cured pain after surgery [8,9,91], but recovery is variable, and the majority of patients continue to demonstrate lower extremity muscle weakness and functional deficits compared to age-matched control persons [92,93,94]. The exercise program could improve these limitations and prepared the persons to become active again in physical activity and sports.

Many studies have been focused on exercise after THR/TKR, but their goals differed from those of the present study. Indeed, the literature often focused on the correction of sarcopenia, neuromuscular function, and pain-induced disuse of the affected leg before and in the first weeks or months immediately after surgery [95,96,97]. Other studies focused on which type of athletic activities (e.g., golf, swimming, tennis, walking, mountaineering, jogging, tennis, gym activities) deemed acceptable in the long-term in order to avoid damages of the implanted arthroplasty [98,99,100]. Nevertheless, the study published regarding sport activity after THR and TKR, there are no recognized criteria for exercise prescription for those who have completed surgical and rehabilitative treatment after THR/TKR, and the workout characteristics are simply based on allowed and not recommended sports activities [31,32]. Thus, this study will investigate the safety and efficacy of an exercise program specifically designed for persons who have completed surgical and rehabilitative treatment after THR/TKR.

Physical activity has a primary role in preventing chronic diseases and their consequences associated with the aging process. Arthrosis is an aging process that leads to pain and, consequently, a state of inactivity. This problem has already been studied in the literature by programs tested in different countries, which aimed to increase physical activity, functional status and improve the response to the surgery [101]. In the case of severe osteoarthrosis, hip or knee replacement reduce pain and improve function; therefore, we would expect a significant change of motor behavior and hypothesis an active lifestyle by these persons [10] after surgery. However, most persons do not increase physical activity from pre-to-post-surgery but remain sedentary and present a high prevalence of diabetes, hypertension [13,17,18,100], and overweight or obesity [102]. Indeed, despite the total knee and hip prostheses lead to global benefits independently of body weight, the risk of disability increases among persons with high BMI following THR and TKR [103,104]; in particular, a higher obesity level correlates with lower post-surgery functional scores [105,106].

Adherence to an exercise program is a crucial aspect of successful training. This protocol includes gym group training because there is evidence that adherence is higher in supervised programs than in those unsupervised, as proved by systematic reviews [107,108,109,110,111]. Group training facilitates participation by reducing costs and promoting social interactions, which lead to improved social, mental, and emotional health [107,108].

Mobility and transport difficulties often preclude regular participation in an exercise program in senior citizens [27,42]. To solve this issue, we selected exercises that can be performed using easily available cheap equipment (elastic bands, yoga mats, dumbbells and soft dumbbells) instead of gym machines. This may facilitate the scaling up of the training program, if proved effective and safe, as it will be possible to replicate it not only in well-equipped gyms but also at home or in suitable spaces close to home. The use of community environments, where gyms are not available, has been reported to be very effective for sustains exercise adherence in previous research [42].

Health related QoL is considered of paramount importance to evaluate the impact of chronic diseases and treatment outcomes [112]. As a primary outcome measure, we selected the SF-36 because it is a multidimensional instrument widely used to evaluate the THR and TKR outcomes (see, e.g., References [113,114]). However, this is a generic instrument which has not been designed to approach QoL aspects specifically related to the evaluation of the outcomes of these surgical procedures. Thus, we included as secondary outcomes a multidimensional system of measures of impairments, functional and clinical status specifically related to the expected effects of the exercise program on the type of persons who are the focus of this study. This could allow a better understanding the results and, if necessary, further optimization of the exercise protocol.

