### 2.4. Sample Size

The sample size was calculated through an a priori power analysis calculated on the study’s primary outcome, the physical health domain of the 36-item Short Form Health Survey (SF-36), assessed at post-surgery baseline and six-month assessments in both intervention and control groups. A randomized controlled pilot study in the literature with a similar rationale [36] was considered as a reference. Starting from this study, in which the SF-36 was used before and three months after the start of the intervention, was found a size effect of 1.06 (considered “increased”) with a standard deviation of 10 for each considered group. The power analysis was performed separately for THR and TKR, using a two-code test for independent groups with an error α = 0.05 and a sampling power (1-β) of 0.8, and a drop-out percentage of 30%. The minimum number required was estimated in 20 patients per group. Considering the four groups evaluated in the present study, two intervention groups (THR or TKR) and the two respective control groups, the final sample size was identified in a total of 80 patients.

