#### 2.6.1. Intervention Groups (IGs)

The intervention groups for THR and TKR will be trained under the direct supervision of a graduate trainer in Sports Science. The protocol aims to reach fitness by improving muscular strength, range of motion (ROM), and muscular elasticity, as well as gait, balance and aerobic capacity. The exercise program is structured in 2 days per week 1 h sessions, and lasts six months. Each session is divided into warm-up, strength, balance, flexibility and cool-down sections. The protocol defines strategies to instruct patients and check the correct and safe execution of the motor tasks for both THR and TKR. 

The exercises are chosen to avoid potentially harmful or painful movements or positions according to the participants’ conditions. For instance, exercises in quadrupedal position are excluded for persons with TKR. Exercises with leg adduction movements and in lateral decubitus positions are excluded for persons with THR. In order to follow the progressive workload adapting criteria, frequency, type, time and duration of the training will be modified based on the functional capacity reached by participants. Only common-use low-cost tools, such as elastic bands, yoga mats, dumbbells and soft dumbbells, are used within the exercise sessions. 

In addition, all persons of the intervention groups will be requested to choose an additional third day of the week to carry out at least one of the following activities: brisk walking, cycling or swimming. The duration of these additional activities will be at least 30 min in order to reach the minimum amount of exercise per week of 150/300 min recommended by WHO [23]. Participants to the intervention group will be monthly request how many hours of additional activities has been done during the last month.

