### 2.8. Statistical Analysis

The qualitative variables will be summarized in terms of frequency, and the quantitative ones in terms of mean and standard deviation for both intervention groups and control groups and for the three times of assessment. To compare characteristics between and within groups the principle of intention to treat will be used, adjusting for adherence to the exercise program. In order to compare the baseline characteristics between the two groups, the following tests will be used: Student’s t-test for parametric quantitative variables; Mann–Whitney test for non-parametric variables; Chi-square test for qualitative dichotomous variables. To compare the changes between and within intervention groups and control groups among baseline and follow-up assessments the following tests will be used: for the normally distributed variables, analyses of variance for repeated measures followed by t-test with Sidak post hoc corrections; for non-parametric variables, the Friedman test followed by the Wilcoxon test with Bonferroni correction.

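### Exercise is delivered in supervised groups in one arm only, but the sample size and named tests treat all patients as independent, so type I error may exceed 0.05 if outcomes correlate within training groups

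*Protocol article*

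**What the plan says.** - **Delivery, intervention arms.** Section 2.6.1 says that hip and knee intervention patients "will be trained under the direct supervision of a graduate trainer in Sports Science", twice a week for six months. The Discussion adds "This protocol includes gym group training", chosen because supervised programmes have better adherence, and remarks that training together brings social and emotional benefit. The Limitation section also refers to group exercise on land.
- **Delivery, control arms.** Section 2.6.2 gives controls usual care with advice and monthly contact, and no structured programme. Any training-group effect can therefore arise in one arm only.
- **Sample size.** Section 2.4 is calculated "using a two-code test for independent groups", with "an error α = 0.05" and "a sampling power (1-β) of 0.8", separately for hip and knee.
- **Analysis.** For normally distributed outcomes section 2.8 names "analyses of variance for repeated measures followed by t-test with Sidak post hoc corrections". For other outcomes it names Friedman and Wilcoxon tests. None of these has a term for training group or trainer.

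**The concern.** Patients who exercise together under one trainer for months can end up more alike than patients treated separately. If so, the mean of the intervention arm varies more than the independent-patients formula allows, while the mean of the control arm does not. The planned tests would then give intervals that are too narrow and reject a true null hypothesis more often than the stated 5%. The result of one unusually good group or trainer could be read as an effect of the programme.

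The Discussion itself describes a route for such correlation: it links group interaction to social, mental and emotional health, and the SF-36 scores all three areas. For the physical health domain, on which the trial is sized, this route is less direct, and a shared trainer is the likelier source.

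**Working it through.** **Step 1: reproduce the plan's figure.** Inputs from section 2.4: "was found a size effect of 1.06", read as a standardised difference; "with a standard deviation of 10 for each considered group"; alpha 0.05, taken as two-sided; power 0.80; drop-out 30%.

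Evaluable n per arm = 2 × ((1.960 + 0.842)/1.06)² = 2 × 6.985 = 13.97, so 14. With drop-out, 14/0.70 = 20. This is the stated 20 per group, so the figure contains no allowance for clustering.

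**Step 2: allow for clustering in one arm.** With groups of size m and intraclass correlation ICC in the intervention arm only:

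- design effect in that arm: DE = 1 + (m − 1) × ICC
- true over naive standard error of the difference: f = √((1 + DE)/2)
- actual two-sided alpha: 2 × (1 − Φ(1.960/f))
- power with 14 evaluable per arm: Φ(1.06/√((1 + DE)/14) − 1.960)
- n per group: (1 + DE) × 6.985, rounded up, then divided by 0.70 and rounded up

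Group size and ICC are **assumptions**; the article gives neither. Example with m = 7 and ICC = 0.05: DE = 1 + 6 × 0.05 = 1.30; f = √(2.30/2) = 1.07; alpha 6.8%; power 74%; n = 2.30 × 6.985 = 16.07, so 17, and 17/0.70 = 24.3, so 25.

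| ICC | m | DE | f | alpha | power | n per group |
|---|---|---|---|---|---|---|
| 0 | any | 1.00 | 1.00 | 5.0% | 80% | 20 |
| 0.02 | 3 | 1.04 | 1.01 | 5.2% | 79% | 22 |
| 0.02 | 10 | 1.18 | 1.04 | 6.1% | 77% | 23 |
| 0.05 | 3 | 1.10 | 1.02 | 5.6% | 78% | 22 |
| 0.05 | 7 | 1.30 | 1.07 | 6.8% | 74% | 25 |
| 0.05 | 10 | 1.45 | 1.11 | 7.7% | 72% | 26 |
| 0.10 | 3 | 1.20 | 1.05 | 6.2% | 76% | 23 |
| 0.10 | 10 | 1.90 | 1.20 | 10.4% | 64% | 30 |

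Part of the step from 20 to 22 is rounding, since 13.97 lies just below 14.

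**Step 3: check by simulation.** The formulas use a normal approximation, which is rough with so few groups. Simulated t-tests (40,000 trials per setting; 2 groups of 7, 2 of 10 or 4 of 5 per joint; equal arms) reject a true null at these rates:

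- ICC 0: about 5.0%
- ICC 0.02: about 5.4% to 6.1%
- ICC 0.05: about 6.1% to 7.8%
- ICC 0.10: about 7.2% to 10.7%

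These agree with the table.

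**Step 4: cost of the alternative model.** A partially nested test, with class variance pooled over hip and knee and Satterthwaite degrees of freedom, was simulated at a true difference of 1.06 SD. With 2 groups of 7 per joint and **no** clustering, power falls from 77% (t-test, 14 per arm) to about 65%. In about 15% of trials the t-test is significant and the nested test is not. The loss depends on how negative variance estimates are handled. At ICC 0.05 the class variance is estimated as zero in about half of the trials. With 4 groups of 5 per joint the loss is small, from about 90% to 87–88%.

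**The case against.** The strongest reply is that the article does not show that any clustering exists. Three parts of it stand.

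- **A reader might infer that the standard errors are too small and that the type I error does exceed 0.05.** The documents do not support this. It needs a positive ICC, and none is given. At ICC 0 nothing changes, and with small groups or a low ICC the effect is trivial.
- **A reader might also infer that patients stay in fixed classes with one trainer for six months.** The article does not say so. Group delivery appears only in the Discussion and its Limitation part; section 2.6.1 describes supervision, not classes. Patients enrol one by one before surgery, so entry may be staggered and membership rolling. Individual adaptation of workload and a self-chosen third activity may also weaken any common effect.
- **The Discussion's case for group training rests on adherence.** Social interaction is a supporting remark, and it bears less on the physical domain that sets the sample size.

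A further reply is that such modelling belongs in an analysis plan that is not shown. This stands only in part. The point is not a missing detail: the article itself fixes an independent-groups sample size and names the tests, and both sit badly with the delivery that it describes. A short methods paragraph does not, however, rule out a sensitivity model.

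**Conclusion.** The point holds in conditional form. Delivery in supervised groups in one arm only is stated, and both the sample size and the named tests assume independent patients. If outcomes correlate positively within training groups, standard errors are too small. Under assumed groups of 3 to 10 and an ICC of 0.02 to 0.10, the type I error is about 5% to 10% and power is about 79% to 64% against a planned 80%. The low end is negligible and the high end would matter. The article gives no basis for choosing within that range, so the finding supports a cheap safeguard, not a claim that the primary analysis is invalid.

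**What to change.** 1. Record training group and trainer for each intervention patient, including changes of group. Report the number and size of groups, the number of trainers, and whether membership was fixed or rolling.
2. Pre-specify one sensitivity analysis of the primary comparison: a partially nested mixed model with a random class effect in the intervention arm only, controls as singletons, small-sample degrees of freedom, and class variance pooled over hip and knee. Report the ICC with its interval.
3. Keep this analysis non-binding. Disagreement between the two models should be reported and discussed, but should not by itself make the primary p-value inconclusive. With few groups the nested test loses much power even when there is no clustering (step 4 of the working).
4. State as a limitation that with only one class per joint, or only one trainer, that class or trainer effect cannot be separated from the programme effect by any model.

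The cost is one identifier on the attendance record and one extra model. The sensitivity interval will be wider, and the ICC will be imprecise. The identifiers are easy to collect during delivery and hard to reconstruct later.

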### Limitation

The final goal of this study is to increase regular physical activity among the persons who underwent THR/TKR. Thus, to detect modifications of lifestyle activity represents an important goal of our project. However, to measure lifestyle activity is not an easy matter and several methods have been proposed including self-report questionnaires, smart phone technology, motion sensors, and pedometers [115]. All these methods have strengths and limitations in terms of methodological effectiveness and feasibility. The use of wearable devices or smart phones can be accurate but not easy to use in long-term study by aged participants. Thus, we decided to use a self-report questionnaire of physical activity (RPAQ) and weekly logs although social desirability may result in over-reporting of PA among participants keen to comply with the intervention aims [116]. These factors will require careful consideration in the interpretation of the results.

The protocol takes into account the duration and number of sessions of rehabilitation which participants have undergone before and after surgery, but not the type and intensity of this treatment. This may weaken the results of the study, as large and consistent evidence has proved the importance of pre- and post-surgery rehabilitation [43]. However, we deemed it unfeasible to reliably control this variable, as rehabilitation treatment will be performed not within the premises of our hospital but at the community level within private or public facilities. Nonetheless, differences in rehabilitation treatment outcomes observed at the post-surgery baseline will be used in the results’ analysis and interpretation.

We excluded people from participation in the study who are unable to walk unassisted for 500 m or have significant pain at rest. This may limit the participation of people who need the exercise the most and weaken the study conclusions. However, people with important functional limitations and/or severe pain are eligible for medical and rehabilitation care or aquatic exercise programs while land-based group exercise could be very problematic or even unsafe.

## 4. Conclusions

Exercise is fundamental to maintain or improve health and prevent disability in subjects who undergo THR/TKR. However, no specific indications on the appropriate exercise program are available for these subjects after the rehabilitation phase. The results of this study could add evidence for clinicians, exercise trainers, and policy makers toward the best strategy to ensure safe and effective exercise after surgery.

## Figures and Tables

**Figure 1 ijerph-18-06732-f001:**
[figure not shown]
Study design.

**Table 1 ijerph-18-06732-t001:** Inclusion and exclusion criteria.

Inclusion Criteria	Exclusion Criteria	
Pre-Surgery Criteria	Pre-Surgery Criteria	Post-Surgery Criteria
Signed informed consent; Age: 50–80 years; Indications: Patient with advanced unilateral osteoarthritis requiring primary THR or TKR; General: ASA ^1^ class 1 or 2;	1. Unable/unwilling to sign the informed consent form of the study and/or willing to comply with the study requests; 2. Poor knowledge of Italian language which prevents understanding of the content of the consent form and/or of instructions for assessment and/or training; 3. Severe functional limitations of other lower extremity joints besides that for which surgery is planned; 4. Impairment of communicative and/or sensory functions so severe to make impossible understanding or executing trainer’s instructions (dementia, aphasia, blindness, deafness); 5. Heart failure (NYHA ^2^ class > 2); 6. Unstable angina; 7. Pulmonary disease requiring oxygen therapy; 8. Symptomatic peripheral arteriopathy; 9. Recent myocardial infarction or hospital admission for any other reason in the previous six months; 10. Symptomatic orthostatic hypotension; 11. Hypertension in poor pharmacologic control (diastolic > 95 mmHg, systolic > 160 mmHg); 12. Relevant neurological condition impairing motor or cognitive function; 13. Any other condition that the medical doctor considers contraindicating the participation in an exercise program of moderate intensity; 14. Severe depression	Functional performance: Able to stand and walk > 500 m independently; Pain: score ≤ 4 in VAS ^3^ during rest.

^1^ ASA: American Society of Anesthesiologists; ^2^ NYHA: New York Heart Association Functional Classification; ^3^ VAS: Visual Analogue Scale.

**Table 2 ijerph-18-06732-t002:** Variables collected during the study and time of recording.

	Assessments			
	before Surgery	after Surgery and Rehab		
		Baseline	3 Months	6 Months
General characteristics				
Age	X			
Gender	X			
Body mass index	X			
Comorbid conditions	X			
Education	X			
Social status	X			
Professional status	X			
Home-Gym Distance (only for intervention groups) Possibility to reach the gym in autonomy		X X		
Rehabilitation treatment (duration and number of sessions)		X		
Rehabilitation treatment				
Before surgery (duration and number of sessions)		X		
After surgery (duration and number of sessions)		X		
Primary outcome				
Quality of life				
Short-Form Health Survey (SF-36)	X	X	X	X
Secondary outcomes				
Impairments, functional and clinical status				
Maximal strength of the lower limb	X	X	X	X
Hip and knee mobility	X	X	X	X
Hand Grip test	X	X	X	X
Visual Analogue Score (VAS)-Pain	X	X	X	X
Time Up and GO (TUG)	X	X	X	X
Single Stance test		X	X	X
30 s Chair-Stand Test (30 s-CST)		X	X	X
Harris Hip Score (HHS) *	X	X	X	X
Hip disability and Osteoarthritis Score (HOOS) *	X	X	X	X
The American Knee Society scoring (KSS) **	X	X	X	X
Knee Injury and Osteoarthritis Outcome Score (KOOS) **	X	X	X	X
The Western Ontario and McMasters Universities Osteoarthritis Index (WOMAC)	X	X	X	X
The High-Activity Arthroplasty Score (HAAS)	X	X	X	X
Lifestyle				
Recent Physical Activity Questionnaire (RPAQ)	X	X	X	X
Weekly physical activity logs		During whole exercise intervention		
PAIR questionnaire for patients’ attitudes toward physical activity		X	X	X
Safety				
Adverse clinical events		X	X	X
Adherence to the exercise program				
Adherence to the exercise program (only for the intervention groups)		During whole exercise intervention		
Patients’ satisfaction (only for the intervention groups)				
Questionnaire on satisfaction of the exercise program				X

* for THR only; ** for TKR only.

## Data Availability

No new data were created or analyzed in this study. Data sharing is not applicable to this article.
